### Data analysis

We will use an intention-to-treat analysis and generalised estimating equations (GEE) assuming a Poisson distribution and an exchangeable correlation structure within a building to evaluate healthcare utilisation, BP and risk assessment scores, as well as to identify factors contributing to these outcomes. Rate of EMS calls will be analysed at the building-level only, using GEE. We will perform pairwise comparisons of outcomes for each month during the preintervention and intervention periods. We will identify trends in the outcomes during the preintervention and postintervention observation periods. Subgroup analysis by clusters (each building) and by location will be performed. The HABiT survey data will be summarised as a numerical score representing the participants’ perceptions and behaviours regarding CVD and diabetes, and analysed with GEEs. The intracluster correlation coefficient (ICC) will be computed to determine the effect of clustering (by the building the participants reside in) on the participants’ scores. Other outcomes will be analysed using descriptive statistics.

All analyses requiring health administrative data will be performed in a two-step process. First, CHAP-EMS data with identifiers will be securely transferred to ICES for health record linkage, as per the participant consent form. Once linked, the data set will be de-identified for subsequent analysis. All analyses will be performed using SPSS V.20. Statistical significance will be set at α=0.05 and adjusted using the Bonferroni method for secondary analyses. Results will be reported as rate ratios, 95% CIs and associated p values.

Twice a month, the CHAP-EMS data will be reviewed and analysed to assess for errors in data entry, and assure fidelity to the planned intervention (eg, monitor referral patterns by EMS personnel and proper use of the screening tools). This trial did not warrant formal externally managed data monitoring, or a formal committee, due to its minimal risks. Instead, interim analysis will be conducted on the process measures to evaluate intervention recruitment and implementation, and to provide regular reports to local stakeholders (eg, EMS, public health, local housing). Collaborative research agreements with local partners (eg, housing) specify that aggregate data will be shared with these local stakeholders. Individual data will not be released without written permission from the participant.

The primary outcome (rates of EMS calls) and secondary outcomes will be analysed at the beginning of the intervention (preintervention data), and after the 12-month intervention period (postintervention data and full data analysis).

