**Methods/analysis:**

This is a pragmatic clustered randomised control trial in four communities across Ontario, Canada. Within each, four to eight seniors’ apartment buildings will be paired and within each pair one building will be randomly assigned to receive the Community Health Assessment Programme through EMS (CHAP-EMS) intervention, while the other building receives no intervention. During the 1-year intervention, paramedics will run weekly sessions in a common area of the building, assessing risk factors for cardiovascular disease, diabetes and falls; providing health education and referrals to community programmes; and communicating results to the participant's primary physician. The primary outcomes are rate of emergency calls per 100 residents, change in blood pressure and change in Canadian Diabetes Risk (CANRISK) score, as collected by the local EMS and study databases. The secondary outcomes are change in health behaviours, measured using a preintervention and postintervention survey and healthcare utilisation, available through administrative databases. Analysis will mainly consist of descriptive statistics and generalised estimating equations, including subgroup cluster analysis.

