The CHAP-EMS pilot was conducted weekly for 1 year in one seniors’ building.^26^ During this period, 79 residents attended the sessions and 48 residents (61%) visited more than once; 40.7% were identified as having undiagnosed elevated BP, and after five visits the mean BP dropped significantly. Similarly, 66.7% of participants had moderate or high risk of developing diabetes, based on their CANRISK score; at their 6-month follow-up, 15% dropped to a lower risk category. Finally, the number of EMS calls decreased by 25% (CI 17.3 to 34.0%) compared to the 12 months preintervention.^26^ Since initial pilot testing was so promising, it is necessary to conduct a robust evaluation of the effectiveness of the CHAP-EMS Programme using randomised controlled trial methodology to understand the effectiveness of CHAP-EMS once scaled up and applied across a number of settings. The evaluation aims to answer the following research questions:

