### Primary questions

Will there be a *difference in the rate of EMS calls* in subsidised seniors’ housing buildings receiving the CHAP-EMS programmes compared to buildings not receiving the programme?Will there be a *change in measured systolic and diastolic BP* in senior residents living in subsidised seniors’ housing after receiving the CHAP-EMS programme compared to their own baseline measurement?Will there be a *difference in 10-year diabetes risk, as measured using the CANRISK tool,* in senior residents living in subsidised seniors’ housing after receiving the CHAP-EMS programme (healthy lifestyle education) compared to their own baseline measurement?

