### Primary and secondary outcome measures

The primary outcome of EMS call rate (number of calls for building made by residents aged 55 years or older per 100 residents aged 55 years or older in the subsidised seniors’ building) will be available for each building from the EMS administrative database. The primary outcomes of change in measured systolic and diastolic BP, and difference in 10-year diabetes risk (CANRISK score), will be available from the measurements entered by the paramedics into the study database. The secondary outcomes will be difference in health perceptions, behaviours, intentions regarding behaviours, health literacy and knowledge of resources, measured by interviewer-led survey preintervention and postintervention; and difference in health-seeking behaviour (eg, number of ED visits/population 55 years and older), which will be based on administrative databases.

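### A Poisson GEE with rate ratios is assigned to BP and CANRISK, primary outcomes defined as change from own baseline: it cannot be fitted to the changes, and on measured levels it gives a ratio of means under the wrong name

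*Protocol article*

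**What the plan says.** The Data analysis section names one model for three kinds of outcome: GEE "assuming a Poisson distribution and an exchangeable correlation structure within a building to evaluate healthcare utilisation, BP and risk assessment scores". It gives one reporting rule: "Results will be reported as rate ratios, 95% CIs and associated p values". No other distribution, link or effect measure is named for BP or for the risk scores.

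The outcomes are defined elsewhere as changes. The abstract states: "The primary outcomes are rate of emergency calls per 100 residents, change in blood pressure and change in Canadian Diabetes Risk (CANRISK) score". The section on primary and secondary outcome measures repeats this with "The primary outcomes of change in measured systolic and diastolic BP" and a difference in CANRISK score. Under Primary questions, both are to be assessed "after receiving the CHAP-EMS programme compared to their own baseline measurement". The Introduction reports for the pilot that "after five visits the mean BP dropped significantly", so the hoped-for BP change is negative.

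**The concern.** BP in mmHg and CANRISK in points are not counts of events over a population or a period. A Poisson distribution has no probability below zero, and its log link forces a positive mean, whereas the programme is meant to produce a negative mean change. The distribution also ties the variance to the mean, which has no basis for a BP reading or a points score. A rate ratio has no meaning for either measure.

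The stated analysis therefore does not match two of the three primary outcome groups. The analyst would have to change the model once the data are in, or report a quantity that does not answer the stated question in its own units. The choice is written into the protocol, so this is not detail left to an analysis plan.

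**Working it through.** The plan states no effect size or SD for BP or CANRISK, so it has no figure to reproduce here. The values below are assumptions, given as ranges where possible.

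**1. Change as the response.** In an intercept-only Poisson GEE with a log link, the estimate solves exp(b) = mean change. If the mean change is negative, no b satisfies this.

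For individual values, assume a mean fall of 5 mmHg and a normal SD of change s. The share of negative changes is Φ(5/s):

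| s (mmHg) | Φ(5/s) |
|---|---|
| 20 | 0.60 |
| 15 | 0.63 |
| 12 | 0.66 |

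A simulation used 24 buildings of 58 residents, mean 140, SD 18 and a true mean fall of 5 mmHg. In it, 62% of changes were negative. The Poisson GEE (exchangeable within building) and the plain Poisson regression both stopped with invalid weights. A Gaussian identity-link GEE fitted the same changes directly: mean change -4.4 mmHg, robust SE 0.42.

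**2. Level as the response, with a before/after term.** The Poisson GEE was fitted to the same simulated data as levels.

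| Model | Estimate | Robust z |
|---|---|---|
| Poisson, log link | ratio 0.968 | -10.6 |
| Gaussian, identity link | -4.4 mmHg | -10.5 |

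The two estimates describe the same fall: 139.17 × 0.9683 = 134.76, and 139.17 - 4.41 = 134.76. The Poisson result is a ratio of mean BP, about 3.2% lower. It is not a ratio of rates.

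**3. Variance assumption.** At mean 140, the Poisson variance divided by the true variance is 140/SD²:

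| SD (mmHg) | 140/SD² |
|---|---|
| 10 | 1.40 |
| 15 | 0.62 |
| 18 | 0.43 |
| 20 | 0.35 |

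**4. Effect on model-based standard errors.** The question is a within-person contrast. With n residents measured twice, the true SE of the mean change is SD of change/√n if clustering of changes by building is ignored. The Poisson model-based SE on the mmHg scale is √(2 × mean × (1 - ICC))/√n, with dispersion fixed at 1 and one exchangeable correlation per building. Taking mean 135 (assumed) and ICC 0.025 (the ceiling in the Sample size section), this is √(2 × 135 × 0.975)/√n = 16.2/√n.

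| SD of change (mmHg) | True SE / model-based SE |
|---|---|
| 12 | 12/16.2 = 0.74 |
| 15 | 15/16.2 = 0.92 |
| 20 | 20/16.2 = 1.23 |

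The model-based SE is too large when the SD of change is below 16.2 and too small above it. Since SD of change = SD × √(2(1 - r)), at SD 18 the switch falls at a within-person correlation of r = 1 - 263.25/(2 × 324) = 0.59.

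**The case against.** The strongest reply is that the Data analysis sentence names BP and risk scores, not changes in them, and that the same section plans comparisons and trends over the periods before and after the programme starts. A GEE on measured levels with a time term is a fair reading. It converges, and a 3.2% lower mean BP can be interpreted. This stands. A reader might infer that the stated model cannot be fitted or interpreted at all, but the documents support that only if the response is the change.

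A reader might also infer that standard errors would be uniformly too small, by 18/11.6 = 1.55 to 20/11.6 = 1.72, where 11.6 = √135. That compares cross-sectional SDs, whereas the question is a within-person contrast. Step 4 shows that the error can go either way. The section also does not say that model-based errors will be used, and robust ones would correct the problem. Robust variance with the building as cluster also allows for repeated readings on one resident, so the working correlation is chiefly a matter of efficiency.

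For the HABiT survey the section names only GEEs, with no distribution. The general reporting sentence cannot cover everything, since some outcomes are to be summarised descriptively. It is not established that the plan assigns Poisson to HABiT.

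Finally, Poisson suits the EMS call rate, which the Sample size section treats as the main outcome. What none of this answers is that the level model still reports a ratio under the name of a rate ratio, for outcomes defined as changes in mmHg or points.

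**Conclusion.** The point holds in a limited form. The Poisson distribution and the rate ratio are stated choices that do not suit BP and CANRISK. For the changes as defined, the model is infeasible: the expected mean BP change is negative, and about 60 to 66% of individual changes would be below zero under the assumed mean fall of 5 mmHg and SD of change of 12 to 20 mmHg. For levels, the model fits and the test is nearly unchanged (z -10.6 against -10.5 in one simulated data set), but the estimate is a mislabelled ratio of means.

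Model-based standard errors would be wrong by a factor of about 0.74 to 1.23 (true over model-based) under the assumptions in step 4. All numerical sizes concern systolic BP and rest on assumed means and SDs. None was worked out for diastolic BP or CANRISK, where the argument is one of principle. The main EMS-call analysis is unaffected.

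**What to change.** In the Data analysis section:

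- Limit the Poisson distribution and rate ratios to EMS calls and other utilisation counts. For the call rate, use as offset the resident denominator already defined under the outcome measures.
- For BP and CANRISK, specify a Gaussian identity-link GEE with robust variance or a linear mixed model. Account for repeated readings within participant and for clustering by building. State whether the response is the change or the level at each time.
- Report mean differences in mmHg or points with 95% CIs. Word the reporting sentence so that rate ratios apply to counts only, which also keeps the HABiT score from being reported as one.

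This takes about two sentences. It needs no extra data and changes no sample-size figure, because none is stated for BP or CANRISK.

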### Allocation of intervention

First, the buildings will be matched into similar pairs based on geographic location, numbers of units within the building, proportion of units occupied by seniors, existing EMS call rate (number of calls/100 apartment units) in the 2 years prior to the intervention period and the types of social programmes offered to residents. Then, for each matched pair, one building will be randomised to receive the intervention and the other will not receive the intervention (control group). Block randomisation will be used with random allocation of the intervention within each block of two buildings.

Residents of the intervention buildings will have access to the CHAP-EMS programme, in additional to their usual medical care and wellness programmes, while residents of control buildings will only have access to their usual medical care and wellness programmes. Since randomisation is occurring at the building-level, it is not expected that providing usual care as the control condition will impact study recruitment, results or interpretation.

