### Control of bias

For the primary outcome of EMS call rate, we will collect at least 1 year of data before the intervention starts and also use a parallel design (for pairwise analysis) to examine the possible effect of seasonality. For the HABiT, participants will not be informed about the group comparisons. Surveys will be anonymous to decrease the possibility of social desirability bias.

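### The EMS call-rate model stops at the building, although randomisation is within matched pairs, and the planned pairwise and pre/post comparisons are not tied to the primary effect estimate

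*Protocol article*

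**What the plan says.** **Design.** Under Allocation of intervention, buildings are matched on location, size, senior occupancy, social programmes and "existing EMS call rate (number of calls/100 apartment units) in the 2 years prior to the intervention period". Then "for each matched pair, one building will be randomised to receive the intervention and the other will not receive the intervention", and "Block randomisation will be used with random allocation of the intervention within each block of two buildings".

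**Effect model.** Under Data analysis, the GEE is specified "assuming a Poisson distribution and an exchangeable correlation structure within a building", and for the main outcome "Rate of EMS calls will be analysed at the building-level only, using GEE".

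**Other comparisons.**
- Study design plans parallel comparisons of intervention and control buildings, and also pre/post comparisons.
- Data analysis adds: "We will perform pairwise comparisons of outcomes for each month during the preintervention and intervention periods".
- Control of bias plans at least one year of prior EMS data and a pairwise analysis, and gives seasonality as the purpose.
- Data analysis also states: "Subgroup analysis by clusters (each building) and by location will be performed".

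**The concern.** The unit of the randomised comparison is the pair, and the pairs were formed partly on the outcome's own history. The dependence structure written down for the analysis ends at the building, so two buildings chosen to resemble each other enter as independent. The text that does mention pairs concerns months and seasonality. It does not say which single contrast gives the primary rate ratio and confidence interval.

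Two forces then act on that interval. Leaving out positive pair correlation makes it too wide. An uncorrected robust standard error on about 24 clusters makes it too narrow. The net direction depends on quantities nobody knows in advance.

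A smaller matter is that each building is in one arm only. A subgroup result for a single building therefore holds a before-after change and no randomised contrast.

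**Working it through.** The article gives no error rate or power for the EMS analysis itself, so there is no figure of its own to reproduce on this point.

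**Inputs from the article (Sample size):** at least 700 residents per arm, 12 or more intervention buildings, 44.06 calls per 100 residents per year, tolerable ICC up to 2.5%, 10% target reduction, 25% pilot reduction.

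**Assumed:** 12 pairs; between-building SD of the log rate 0.15 to 0.50; 0, 30% or 60% of that variance shared within a pair; 80% of building variance stable over time; two baseline years.

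**Step 1, size of a building.** 700/12 = 58.3 residents. 58.3 × 0.4406 = 25.7 calls a year, or 2.1 a month. The Poisson part of the variance of a log annual rate is about 1/25.7 = 0.039. Monthly comparisons on two calls per building cannot carry the main inference.

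**Step 2, an anchor for building variance.** For counts per resident, ICC = CV²λ²/(CV²λ² + λ), so CV² = [ICC/(1 − ICC)]/λ = (0.025/0.975)/0.4406 = 0.058 and CV = 0.24. The 2.5% is a limit said to be tolerable, not an estimate.

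**Step 3, hand calculation for a post-only comparison.**
- The uncorrected robust variance divides by 12 instead of 11 in each arm, so the standard error is multiplied by √(11/12) = 0.957.
- The effective critical value is 1.96 × 0.957 = 1.877. On 22 degrees of freedom that is a two-sided error of 7.4%.
- Matching shrinks the true variance by (1 − ρ), where ρ = shared fraction × 0.058/(0.058 + 0.039) = shared fraction × 0.60.
- At 30% shared, ρ = 0.18 and 1.877/√0.82 = 2.07, giving about 5.0%.
- At 60% shared, ρ = 0.36 and 1.877/√0.64 = 2.35, giving about 3%.

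**Step 4, simulated type I error, 12 pairs, SD 0.24.**

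| Variance shared in pair | Post-only GEE, plain robust z | Paired t | Paired t + baseline |
|---|---|---|---|
| 0 | 7.6% | 4.7% | 4.9% |
| 30% | 5.0% | 4.7% | 4.6% |
| 60% | 3.2% | 5.0% | 5.4% |

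- Over SD 0.15 to 0.50, the post-only GEE ranges from 1.8% to 8.2% and the paired tests from 4.3% to 5.4%.
- A pre/post GEE (arm by period) with plain z gives 7.4% to 8.5% at CV 0.24 and 0.40, whatever the pair correlation. With a simple t correction it gives 5.0% to 5.8%.
- Adding only the pair or only the baseline rate to a plain-z GEE does not cure the error: 7.4% to 9.0% at SD 0.24.

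**Step 5, power at rate ratio 0.75, 60% shared, 12 pairs.**

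| SD | Post-only GEE | Paired t | Paired t + baseline |
|---|---|---|---|
| 0.24 | 65% | 68% | 64% |
| 0.30 | 52% | 60% | 58% |
| 0.50 | 25% | 39% | 40% |

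A separate run at CV 0.40 gave 37%, 48% and 54% for these three, and 60% for the t-corrected pre/post GEE. At the planned 10% reduction and SD 0.24, the three tests in the table reach only 11% to 17% across pair correlations. The choice of analysis does not rescue power for that effect.

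**The case against.** The strongest reply is that the article fixes only a model family, a distribution and a working correlation. It lists no covariates, not even arm, and it expects the GEE to identify contributing factors. Pair terms, baseline covariates and small-sample corrections commonly sit in an analysis plan that is not shown. **This stands as far as it goes:** their absence alone is no finding. The point rests on what is written, namely a dependence structure that does not follow the randomisation and pairwise comparisons assigned to other purposes.

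A second reply is that correlation within a building makes sense only with repeated records per building, so a pre/post GEE is the natural reading. In that model the arm-by-period contrast removes stable building and pair effects. **This also stands in large part.** Without a pair term, the t-corrected version matched or beat the paired-plus-baseline test on power in the scenarios compared. It does not remove the small-sample problem, which stays at about 7.5% to 8% with plain z.

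A reader might infer that the plan breaks the matching and ignores the baseline rate. The documents do not support that: Study design, Data analysis and Control of bias all plan pairwise, pre/post or prior-year comparisons. Nor do they support saying that the error rate is necessarily wrong or that power is necessarily lost. With 30% shared variance, the post-only error is close to 5%.

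Per-building results may be meant as descriptive. If so, the article should say so.

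**Conclusion.** The point holds in a limited form. The stated EMS model does not visibly follow the matched-pair randomisation, and the article does not say which of its several comparisons yields the primary estimate.

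If ordinary large-sample inference is used with about 24 buildings, the nominal 5% can be roughly 2% to 8% for a post-only analysis and 7.5% to 8% for a pre/post GEE. A value near 5% in the post-only case comes from two opposing errors cancelling, which cannot be relied on. The article itself says that no literature gives an ICC for a similar study.

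The power cost of an unmatched post-only analysis is at most about 3 points at SD 0.24. It is about 15 points at SD 0.50 with 60% shared variance, and there is little or none when matching is weak. These sizes depend on the assumed building variance, pair correlation and stability over time.

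**What to change.** Name one primary contrast for EMS calls over the 12 intervention months that uses the pre-intervention call rate and has valid small-sample inference. Any of these would serve:

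- within-pair log rate ratios, adjusted for the within-pair difference in log baseline rate, with a t reference on pairs minus 2 degrees of freedom;
- a within-pair re-randomisation test;
- a pre/post arm-by-period GEE with a small-sample-corrected standard error and a t reference.

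Label the monthly pairwise comparisons and the per-building results as descriptive. Report treatment effects by matched pair and by location, the latter with an arm-by-location interaction.

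**Cost:** wording only, since the baseline and intervention-period call data are already to be collected. A few degrees of freedom are spent. A baseline term can lose a little power when pairs are few and buildings vary little: with 8 pairs, SD 0.24 and 60% shared variance, power at rate ratio 0.75 fell from 43% (paired t) to 38% (paired t with baseline).

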### Sample size

Given that our main outcome will be rates of calls per 100 residents per year, we calculated our sample size using the formula for the Poisson test. Based on data from the Hamilton Paramedic Services, the average rate of calls for our pilot sample was 44.06 EMS calls per year per 100 residents older than 65 years. If we assume a difference of 10% (a difference of 4.4 EMS calls per 100 residents per year) between the intervention and control groups, with 0.8 β and α of 0.05, we would need a sample of 131 per group. This is a conservative estimate of effect size since the pilot study showed a 25% reduction in EMS calls.^26^ Also, a difference of 10% is considered operationally significant by Hamilton Paramedic Services (personal communication with [name]). This is likely to be significant in other Ontario localities as well.

The overall sample size will be a minimum of 700 participants per arm (intervention or control) in 12 or more intervention buildings across all sites. Considering the Design Effect (cluster sampling by buildings), we can accommodate an intracluster correlation coefficient (ICC) of up to 2.5% given our proposed sample size. There is no literature regarding an ICC for a similar study.

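### Monthly pairwise comparisons of the EMS call rate are planned with p values, but the plan does not say whether its Bonferroni rule covers them, and no single month has useful power

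*Protocol article*

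**What the plan says.** All references are to the protocol article.

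- **Data analysis, main model.** "Rate of EMS calls will be analysed at the building-level only, using GEE". The section plans GEE with a Poisson distribution and exchangeable correlation within a building.
- **Data analysis, monthly comparisons.** "We will perform pairwise comparisons of outcomes for each month during the preintervention and intervention periods". Trends over time and subgroup analyses by building and location follow.
- **Data analysis, error rate.** "Statistical significance will be set at α=0.05 and adjusted using the Bonferroni method for secondary analyses". The section then says results will be given as rate ratios with 95% confidence intervals and p values. It makes no exception for the monthly comparisons.
- **Data analysis, timing.** The EMS rate is analysed at the start of the intervention and "after the 12-month intervention period (postintervention data and full data analysis".
- **Sample size.** The trial is sized on "rates of calls per 100 residents per year", not on a monthly rate.
- **Control of bias.** At least one year of preintervention EMS data will be collected. The pairwise analysis of the EMS rate is linked to examining seasonality.

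**The concern.** The monthly sentence refers to outcomes in general, but among the primary outcomes it can only concern the EMS rate. Blood pressure and CANRISK are measured at programme sessions, CANRISK is repeated only every six months, and residents of control buildings are contacted only for surveys. Control of bias confirms the link between the pairwise analysis and the EMS rate.

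With at least 12 preintervention months and 12 intervention months, the plan produces at least 24 monthly comparisons of a primary outcome. Whether they are adjusted depends on whether they count as secondary analyses, which the text leaves open. On one reading there are many unadjusted chances of a significant month. On the other, the tests are so strict that they can show nothing. Neither reading gives a useful test of the programme. On the unadjusted reading, a favourable month could be reported as a result on the main outcome.

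**Working it through.** **The plan's own figures.** The article gives no figure for the monthly comparisons. Its target difference reproduces: 10% of 44.06 is 4.4 calls per 100 residents per year. Its sample size of 131 per group does not. The two-sample Poisson formula (1.96 + 0.84)² × (0.4406 + 0.3965)/(0.4406 − 0.3965)² gives about 3,385 per group, two-sided. That is a separate matter, and 131 is not used below.

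**Inputs** (Sample size, unless noted)
- Control rate: "44.06 EMS calls per year per 100 residents older than 65 years", that is 0.4406 per resident-year. This is a pilot figure for an older group than the trial's residents aged 55 and over.
- Effect: 10% reduction. The pilot showed 25%.
- Size: at least 700 per arm and at least 12 intervention buildings, so 700/12 = 58.3 residents per building.
- α = 0.05 (Data analysis), taken as two-sided because sidedness is not stated.

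**Step 1: calls per month.**
- Per arm: 700 × 0.4406/12 = 25.7.
- Per building: 25.7/12 = 2.14. The abstract's four communities with four to eight buildings each imply 8 to 16 intervention buildings, which gives 25.7/16 = 1.6 to 25.7/8 = 3.2.

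**Step 2: power of one month, whole arms, α = 0.05.**
- Expected counts are 25.7 and 25.7 × 0.9 = 23.1.
- SE(log RR) = √(1/25.7 + 1/23.1) = 0.287.
- |log 0.9|/0.287 = 0.105/0.287 = 0.37.
- Power = Φ(0.37 − 1.96) + Φ(−0.37 − 1.96) = 6.6%.
- Enumerating the two Poisson counts gives 6.5% (Wald test) or 4.9% (exact conditional test). For a 25% reduction it gives 15.8% or 12.7%.
- The 95% interval for the rate ratio extends by a factor exp(1.96 × 0.287) = 1.75 each way.
- These figures ignore clustering. With the plan's maximum ICC, the design effect is 1 + 57.3 × 0.025 = 2.43. As an illustration, the chance of rejecting in the right direction then falls from Φ(0.37 − 1.96) = 5.6% to Φ(0.37/√2.43 − 1.96) = 4.2%.
- Doubling the residents changes little: SE = 0.287/√2 = 0.203 and power is about 8%.

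**Step 3: if Bonferroni does not cover the months.** Chance of at least one false positive with k independent tests of size 0.05:
- k = 12: 1 − 0.95¹² = 46%.
- k = 24: 1 − 0.95²⁴ = 71%.

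**Step 4: if Bonferroni covers them with divisor 24.** The level is 0.05/24 = 0.0021, and familywise error is at most 5%. Arm-level power in one month is then:

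| True reduction | Exact | Wald |
|---|---|---|
| 10% | 0.2% | 0.3% |
| 25% | 1.1% | 1.5% |

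**Step 5: reduction needed for 80% power in one month**, from Φ(μ(1 − r)/√(μ(1 + r)) − z) with μ = 25.7: about 65% at level 0.05 (r = 0.35) and about 84% at 0.05/24 (r = 0.16).

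**Step 6: one building pair.** With 2.14 expected calls in each building, a test at 0.05 has a true size of 0.6% (exact) or 4.3% (Wald). Power for a 10% reduction is 0.6% or 4.3%, no better than the size.

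**The case against.** The strongest defence has four parts.

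1. **There is multiplicity control.** The Bonferroni rule speaks of secondary analyses, not secondary outcomes. The monthly comparisons come after the building-level GEE and can naturally be read as secondary. This stands. A reader might infer that the monthly tests have no multiplicity control and that chance findings are therefore likely, but the document does not support that. It supports only that the scope of the rule and its divisor are not stated.
2. **The plan points to an annual comparison.** The sample size uses a yearly rate, the EMS rate is assigned to GEE, and the full analysis comes after 12 months. No section makes a single month decisive. This also stands. A reader might infer that the trial cannot detect a real effect, but the low power shown here belongs to single months and not to the 12-month GEE.
3. **Preintervention months have a purpose.** Control of bias gives it as seasonality, and buildings are matched on prior call rate. So it would be wrong to say that those comparisons answer nothing. However, seasonality and baseline balance can be shown without month-by-month p values, and a concurrent 12-month comparison already covers the same seasons in both arms.
4. **The unit is not stated.** Pairwise could mean matched buildings or arms. The 46% and 71% are arm-level figures and do not follow from two calls per building, where an exact test seldom rejects. This stands as a limit on those figures.

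An article may also leave the detailed model to a fuller document. Here, though, the article itself commits to the monthly comparisons, so the point concerns a stated analysis and not an omitted detail.

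**Conclusion.** The point holds in limited form. The plan commits to monthly comparisons of a primary outcome, exempts nothing from p values, and leaves unclear whether they are adjusted. Unadjusted, 12 to 24 arm-level tests carry a 46% to 71% chance of at least one false positive. Dependence between months, or a test whose size is well below 0.05, would change these figures. Adjusted for 24 tests, power for a 10% reduction in one month is about 0.2% to 0.3%. Even at 0.05 it is about 5% to 7% before any design effect.

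These results rest on the stated minimums (700 per arm, 12 buildings) and on the pilot rate in residents older than 65. The power conclusion is not sensitive to them, since twice the residents would give about 8%.

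The effect is confined to a supplementary analysis. The 12-month building-level GEE is untouched by this point, which is not a statement about how well that analysis is powered. The change is still worth making, because the comparisons concern the main outcome and could be reported selectively.

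**What to change.** In Data analysis:

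- State that the EMS outcome is decided by one intervention-to-control rate ratio over the full 12 intervention months, from the building-level GEE, adjusted for the preintervention call rate that the trial already collects.
- Replace the monthly comparisons with a descriptive display of monthly rates by arm, including preintervention months to show seasonality, without p values.
- If the timing of an effect is of interest, fit one treatment-by-time term and name it as a secondary analysis under the Bonferroni rule.

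This changes wording only and needs no further data. The cost is that the trial can make no formal claim about a particular month, which the monthly counts could not support in any case.
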